# RAPTOR: Randomised Controlled Trial of PENTOCLO (pentoxifylline-tocopherol-clodronate) in Mandibular Osteoradionecrosis—study protocol for an open-label phase II randomised controlled superiority trial

**DOI:** 10.1186/s13063-025-08966-9

**Published:** 2025-07-24

**Keywords:** Mandible, Osteoradionecrosis, Radiotherapy, Head and neck, Cancer, PENTOCLO, Pentoxifylline, Tocopherol, Sodium clodronate, Clinical trial

## Abstract

**Background:**

Mandibular osteoradionecrosis (ORN) is a severe late radiation toxicity affecting 5–10% of patients who receive radiotherapy as part of treatment for head and neck malignancy. ORN can cause permanent disfigurement, dysfunction, pain and infection. There remains little robust evidence supporting the efficacy of medical or surgical management currently offered in clinical practice. Retrospective case series and meta-analyses of observational studies suggest that a repurposed triple drug combination pentoxifylline-tocopherol-clodronate (‘PENTOCLO’) may be effective in preventing deterioration, promoting healing and ultimately reducing the need for major reconstructive surgery.

**Methods:**

The RAPTOR trial is a phase II, open-label, multicentre, randomised controlled trial with a superiority design. Eligible subjects with mandibular ORN are randomised 1:1 to receive standard of care (Arm A) or PENTOCLO plus standard of care (Arm B) for 12 months. The primary outcome measure is time from randomisation to healing of ORN (without the need for surgery), as measured by clinical examination (confirming completely healed oral mucosa), intra-oral clinical photographs and imaging. RAPTOR has an embedded translational sample collection and a methodological component exploring the use of electronic patient-reported outcome measures (ePROM).

**Discussion:**

The RAPTOR trial is the first randomised controlled clinical trial of PENTOCLO in this clinical setting. The results of this phase II trial will provide robust preliminary evidence on its efficacy and inform the feasibility and appropriateness of a subsequent definitive trial.

**Trial registration:**

RAPTOR is registered with the ISRCTN registry effective date 11th November 2022: Clinical trial of the non-surgical management of radiotherapy damage to the lower jaw ISRCTN34217298, and also registered with the European Clinical Trials Database (Eudra-CT 2022–000728-39).

**Supplementary Information:**

The online version contains supplementary material available at 10.1186/s13063-025-08966-9.

## Introduction

### Background and rationale {6a}

Osteoradionecrosis (ORN) is defined as exposed irradiated bone that fails to heal over a period of 3 months in the absence of recurrent malignancy [1]. For many affected patients, ORN represents a devastating complication of radiotherapy, often causing intractable pain, repeated infection, jaw fracture, fistulation, disfigurement and dysfunction. This can lead to malnutrition, opiate dependency and for a proportion of patients, eventually death.

Current clinical management includes symptomatic or conservative care which includes analgesia, control of infection with chlorhexidine mouthwash, antibiotics, alleviation of any trauma caused by sharp or mobile bone sequestrum using minor outpatient interventions, using, at most, local anaesthetic. Other accepted treatment includes surgical intervention, involving complete resection of all involved bone and reconstruction as necessary [2, 3]. Surgery is a major and invasive intervention, often requiring 8–10 h and multiple surgeons, usually requiring free flap/microvascular anastomosis reconstruction and involving critical care admission and significant hospital stay; it has a high cost and significant complication rate [4]. Surgery of this nature is usually reserved as a ‘last resort’ for patients with worsening and otherwise unmanageable symptoms or increasing extent of ORN. Understandably, there is a focus on the potential for medical management of ORN that may prevent worsening and avoid such major surgery.

Medical management of mandibular osteoradionecrosis using courses of hyperbaric oxygen (HBO) or repurposed drug combinations have been explored. Recent clinical trials indicate that hyperbaric oxygen, is largely ineffective in preventing [5] or treating [6, 7] ORN. A repurposed drug combination pentoxifylline-tocopherol-clodronate (‘PENTOCLO’) [3] has been proposed as a potential pharmacological action. The pentoxifylline-tocopherol combination is thought to reverse soft tissue fibrosis induced by radiotherapy [8]. Potentiation of this combination by clodronate is indicated for osseous lesions, such as ORN of the mandible [9], without resorting to surgical resection and reconstruction. The pathophysiology and potential therapeutic opportunities in ORN have been reframed in recent years, aligned with the use of PENTOCLO, as a fibro-atrophic process. This is thought to be mediated by reactive oxygen species (ROS), a progressively fibroblastic stroma and emphasising the role of TGF-B1 [10]. Pentoxifylline, previously used to treat peripheral vascular disease, has been shown to have in-vivo anti-TNF alpha effect, to increase erythrocyte flexibility, increase vasodilation and to have anti-inflammatory effects [11]. As a single agent pentoxifylline has demonstrated some beneficial effects in soft tissue necrosis and trismus and various functional/symptomatic effects after radiotherapy in breast and head and neck cancer survivors [12]. Tocopherol acts as a ROS scavenger and an inhibitor of TGF-beta1 and procollagen gene expression, but alone has proved ineffective in the management of radiation-induced fibrosis. Combining the two agents, and exploiting their apparently synergistic mechanisms, the combination of pentoxifylline and tocopherol has demonstrated benefit in placebo-controlled trials [8] of radiation fibrosis and necrosis, although appears to need at least 12 months of continuous treatment to avoid rebound. Data on osseous lesions such as mandibular ORN has suggested adding clodronate to inhibit osteoclasts, which may potentiate the effectiveness of the protocol and this current triple regimen (termed PENTOCLO) has been used increasingly since 2005 [3]. Clodronate is a first-generation, non-nitrogenous, oral bisphosphonate, which specifically is not associated with drug-induced osteonecrosis. Clodronate reduces osteoclast activity, decreases fibroblast and macrophage proliferation, and promotes bone formation by osteoblasts. This combination has shown promise in medical management of ORN, with the necrotic bone forming a sequestrum that is eventually shed, revealing intact underlying mucosa.

There are to date no published randomised or controlled clinical trials of PENTOCLO in mandibular ORN. There is some evidence defining some therapeutic effect from retrospective case series and metanalyses. In a single-site, one-arm design, Delanian et al. [9] showed 54 patients with ORN experienced complete resolution of early ORN after a median of 9 months treatment with the PENTOCLO protocol. The available retrospective evidence has been subject to systematic review by two groups, with broadly similar conclusions. Martos-Fernandez et.al [13]. analysed 10 published series with a total of 334 patients included, finding all studies of a low or moderate methodological quality. Little numerical analysis was attempted with a largely descriptive methodology, but it was found that resolution occurred between 3 and 13 months, with 60% of patients showing clinical improvement or total healing. Healing in more advanced cases (Notani Grade 3) is less predictable and may take longer. Heterogeneity in methodology and endpoints was a barrier to further quantitative analyses. Kolokythas et al. [14] studied 7 reports of 186 patients using tighter inclusion criteria. 126 patients fully recovered or improved significantly, ORN was stable or progressive in 60 patients, with 15 patients receiving jaw resections. The estimated proportions of full resolution were 62.7%; of reduction in SOMA score were 86.5%; and of reduction of area exposed bone were 62.0%. Challenges in analysis were created by a lack of standardisation of treatment and outcome reporting. Both reviews concluded that patients tolerated PENTOCLO well, the commonest side effect being mild gastrointestinal disturbance.

### Objectives {7}

A rigorous evaluation of PENTOCLO in the management of ORN of the mandible is now necessary. The primary objective of RAPTOR is to determine if PENTOCLO triple therapy is effective in healing of mandibular ORN. This phase II trial is designed to establish the first robust signal of efficacy, an estimate of effect size, and the safety/tolerability of PENTOCLO in mandibular ORN. Additionally, a repository of blood samples from the trial will allow future studies to explore the genomic determinants of susceptibility to osteoradionecrosis [15, 16]. The results will also provide robust preliminary evidence on its efficacy and inform the feasibility and appropriateness of a subsequent definitive trial.

### Trial design {8}

The RAPTOR trial (Randomised Controlled Trial of PENTOCLO in Mandibular Osteoradionecrosis) is a phase II multicentre, open-label, randomised, controlled, superiority trial of PENTOCLO versus standard of care in patients who have mandibular ORN. The trial protocol was conceived, refined, funded and is being managed with the involvement of patient representatives. The trial has embedded translational and methodological endpoints.

## Methods: participants, interventions and outcomes

### Study setting {9}

Suitable patients will be recruited from surgical, oncology and dental follow-up clinics within UK head and neck oncology multi-disciplinary teams. The list of participating sites is available at the trial webpage [17].

#### Eligibility criteria {10}

Patients must have had prior radiotherapy to the mandible, have diagnosed ORN of the mandible and be considered suitable for medical management. A detailed list of exclusion criteria is given in Table 1. Although definitions of ORN differ, for the purposes of the RAPTOR trial, eligible patients must have exposed mandibular bone either intra- or extra-orally. ORN is classified on clinical and radiographic grounds, from an orthopantomogram (OPT) using a modified version of the Notani Classification [1, 18], and this eligibility and classification of ORN for RAPTOR trial purposes is explained in Fig. 1. Notani class 3 cases are excluded if they have a pathological fracture on clinical assessment, including radiograph, but otherwise may be included. Patients with minor bone spicules (< 20mm^2^) within 12 months of dental extraction/surgery are very likely to heal spontaneously and thus are excluded from the RAPTOR trial. If ORN occurs spontaneously, then patients may be eligible irrespective of the surface area measurements of exposed bone.

**Table 1 Tab1:** Detailed exclusion criteria RAPTOR trial

1. Cannot swallow tablets
2. Prior treatment with PENTOCLO or any element thereof within 12 months of the date of randomisation (4 months, if the PENTCLO is given for ORN prophylaxis reasons at time of dental extractions)
3. Very early ORN after surgery, defined as <20 mm^2^ exposed bone occurring within 12 months of a dental extraction or other dentoalveolar operation
4. Mandibular pathological fracture secondary to ORN
5. Mandibular pathological fracture secondary to ORN
6. Patient has had definitive resection/reconstruction for mandibular ORN—i.e. no longer has exposed necrotic bone present
7. Pregnancy
8. Lactation
9. Age <18 years
10. Acute infection at site of the necrotic bone
11. Hypersensitivity to other methylxanthines
12. Hypocalcaemia
13. Participants not willing to follow the contraceptive requirements of the protocol
14. Contraindications to PENTOCLO medications:
a. Known hypersensitivity, allergy or anaphylaxis to pentoxifylline, tocopherol or sodium clodronate
b. Treated hypotension
c. Severe coronary artery disease, defined as grade IV of the Canadian Cardiology Society Angina Grading
d. Severe cardiac arrythmia, defined as those cases with attributable syncope or heart failure associated; or those with frequent and symptomatic palpitations, breathlessness, dizziness, chest pain, weakness or fatigue.
e. Myocardial infarction within 6 months
f. Prior history of extensive retinal haemorrhage
g. Prior history of intracranial bleeding
h. Impaired renal function (creatinine clearance <30 ml/min, will be formally assessed only if U&E out of reference)
i. Severe liver failure (class B or C Pugh-Child score, will be formally assessed only if LFT values out of reference)
j. Concomitant prescription of anti-platelet agents: clopidogrel, eptifibatide, tirofiban, epoprostenol, iloprost, abciximab, anagrelide, NSAIDs, acetylsalicylates (ASA/LAS) including aspirin >75 mg*, ticlopidine, dipyridamole. (*low dose ≤75 mg aspirin is permitted)
k. Concomitant prescription of ketorolac, cimetidine, ciprofloxacin, theophylline, estramustine phosphate
l. Hereditary fructose intolerance, glucose-galactose malabsorption or sucrase-isomaltase insufficiency
m. Concomitant prescription other bisphosphonates e.g. risedronate, alendronate, aIbandronate, zoledronic acid, pamidronate, etidronate or prescription of denosusamab
15. n. Concomitant prescription of aminoglycoside antibiotics e.g. gentamicin, tobramycin, amikacin, plazomicin, streptomycin, neomycin, paromomycin

**Fig. 1 Fig1:**
[figure not shown]
Eligibility and classification of ORN for RAPTOR trial

### Who will take informed consent? {26a}

Written and informed consent will be obtained from participants along with agreement of the participant to comply with the requirements of the study. Informed consent will be obtained by the site principal investigator (PI) or other appropriately qualified member of the research team who has been delegated this responsibility.

### Additional consent provisions for collection and use of participant data and biological specimens {26b}

In addition, participants will have the option to consent to their data and/or blood samples being used in future research. Consent is also required for screening procedures, explicitly detailing that DNA is to be extracted and stored from a blood test for genomic sequencing as part of ongoing radiogenomic research.

## Interventions

### Explanation for the choice of comparators {6b}

The control arm (A) reflects standard of care management of mandibular ORN in the UK. The intervention arm (B, PENTOCLO) reflects a protocol previously proposed in single-arm ORN studies [9] and that has most widely been adopted for use in ORN in the United Kingdom [3].

### Intervention description {11a}

#### Arm A (control arm, standardised supportive care (SSC))

Arm A (control arm, standardised supportive care (SSC)) may include analgesia, mouthwash, antibiotics and alleviation of local trauma, and any other appropriate measures determined by the site clinician. It specifically excludes hyperbaric oxygen and operations including surgical resection of the mandible (rim or segment). Patients with loose or sharp bone sequestrae or teeth may receive minor debridement or extractions in the outpatient setting to alleviate trauma to the oral soft tissues. This may be with the aid of local anaesthetic as needed. This excludes more major surgery to excise bone that would be carried out in an operating theatre, using saws or drills, or requiring general anaesthetic. Placebo drugs are not used.

#### Arm B (intervention arm, PENTOCLO)

Arm B (intervention arm, PENTOCLO) includes the components of SSC as described above *and*: Pentoxifylline 800 mg daily, Tocopherol 1000 mg daily, Clodronate 1600 mg days 1–5 of 7 (Monday through Friday only).

#### Patient preference phase

The trial also includes a patient preference phase which is available to all participants reaching the 12-month primary follow-up timepoint. At this point, they may elect to conclude their participation in the trial and then return to standard care outside of the trial. Alternatively, they may continue with trial treatments and 3-monthly observations. Patients who choose to continue with trial treatments may choose either to continue with their allocated arm or to switch to the alternative arm of RAPTOR. Observations will continue to the point they wish to withdraw or the point that the trial closes to recruitment. Only one such switch is permissible in-trial. The data within the patient preference phase will be analysed as a secondary endpoint and considered distinctly from the randomised portion of the trial.

### Criteria for discontinuing or modifying allocated interventions {11b}

#### Arm B: dose modifications

In the event of gastrointestinal side effects such as diarrhoea, nausea or vomiting, a divided dose regimen of sodium clodronate may first be considered. In the event of dizziness, headache, epigastric pain or nausea, a temporary 2-week dose reduction of pentoxifylline may additionally (if overlapping symptoms) or alternatively be implemented. If in either case further modification is required, halving the dose of the relevant drug may be considered in discussion with the chief investigator. Detailed specifics of administration and permitted dose modifications are detailed in full in the protocol (available at RAPTOR trial webpage [17]). Patients may discontinue treatment in Arm B in the case of unacceptable toxicity should the possible mitigations not prove tolerable. Discontinuation from PENTOCLO does not trigger discontinuation of the study altogether, and the remaining study procedures, follow-up assessment/visits, and data collection should be completed as indicated in the protocol.

#### Worsening ORN

For either arm A or B (or in patient preference phase), if ORN deteriorates to the point that medical management is no longer indicated, the patient will progress to surgical resection and reconstruction of necrotic bone. After this surgery, it is presumed that there will no longer be remaining necrotic bone to monitor on trial, so this will lead to discontinuation of the study and thus the decision will trigger the Study Completion Visit.

Additionally, patients may discontinue treatment for reasons including intercurrent illness, pregnancy, death, clinician-led assessment of patients’ condition, non-adherence, newly developed or previously unrecognised exclusion criterion.

### Strategies to improve adherence to interventions {11c}

Patient symptoms are collected using a smartphone application (ePROM) as below, which may act as a prompt to improve compliance. In arm B, drugs are dispensed at 3-monthly intervals. A telephone check on adherence is carried out at 2 weeks.

### Relevant concomitant care permitted or prohibited during the trial {11d}

#### Prescribed medicines

A complete list of prohibited concomitant medications is included in Table 1.

##### Surgery

Minor debridement or dental extractions in the outpatient setting are permitted during the trial in either arm, as described above. Formal surgical resection and or reconstruction of ORN leads to discontinuation of the study protocol at that point, also as described above.

### Provisions for post-trial care {30}

The trial also includes a patient preference phase which is available to all patients reaching the 12-month primary follow-up timepoint, as described above. After study completion, patients will return to standard of care for the management of osteoradionecrosis as clinically necessitated and determined by site clinicians.

### Outcomes {12}

The primary outcome measure is time from randomisation to healing of ORN (without the need for surgery), as measured by:Clinical examination by confirming completely healed oral mucosaIntra-oral clinical photographsRadiographs

Conversely, patients who demonstrate failure of treatment as below will be treated as censored observations:Deterioration of ORN including fractureA clinical indication to intervene with mandibular resection and reconstruction

Thus, either the diagnosis of complete healing at 12 months or mandibular fracture or other clinical indication to progress to surgery within 12 months both constitute a primary endpoint for that patient. Other patients whose ORN persists without the need for surgery will also reach the primary endpoint at 12 months, and any change in grade of ORN will be recorded as a secondary endpoint (as below Table 2).

**Table 2 Tab2:** Secondary outcome measures RAPTOR trial

Objectives	Outcome measures	Time point(s) of evaluation
Efficacy:		
1. Deterioration of ORN	Time from randomisation to worsening of ORN as measured: • Extent of exposed bone measured in two dimensions as mm^2^ (and for some trial visits supported by clinical photograph with in-field ruler) and • Notani grade	Every 3 months following randomisation until end of trial for that patient
2. Patients’ analgesia and antibiotic use	• Drug and dose taken for pain relief in the 24-h period leading up to appointment • Days of antibiotic usage. Systemic antibiotics taken since last trial appointment (type, dose and number of days for each type)	Every 3 months following randomisation until end of trial for that patient
3. Patients’ anthropological measurements	Patient BMI (kg/m^2^) where kg is a patient weight in kilograms and m^2^ is their height in metres squared	Every 3 months following randomisation until end of trial for that patient
4. Severity of disease	Grade by “Osteonecrosis of jaw” within CTCAE v 5.0 2017	Every 3 months following randomisation until end of trial for that patient
5. Quality of life	Quality of Life (EORTC QLQ-C30 and QLQ-H&N35)	Every 3 months following randomisation until end of trial for that patient
6. Mandibular preservation	Mandibular preservation rate measured as the removal of mandibula following surgery (segmental resection, with or without reconstruction)	Every 3 months following randomisation until end of trial for that patient
Toxicity:		
7. Gastrointestinal tolerability of PENTOCLO regimen 2 weeks after commencing (Only in Arm B: PENTOCLO)	Gastrointestinal tolerability, as defined by CTCAE grading	2 weeks after commencing trial medications ± 5 working days, (may be by telephone)
8. Compliance	Evaluation of compliance to the IMP	Every 3 months following randomisation until the end of trial for that patient
9. Assessment of IMP’s combination safety	Evaluation of severe adverse events (severe AEs) and/or serious adverse events (SAEs) considered related to the study treatment	Every 3 months following randomisation until the end of trial for that patient
Exploratory:		
10. Patients’ pain and mouth function	• Pain • Eating • Mouth opening • Problems with teeth/gum • Painkillers used • Interference of these symptoms with patients’ daily activities	Every 15 days until end of trial (for that patient) Collected remotely on smartphone App

To avoid any potential risk of bias due to unblinded site investigators, OPT and clinical photographs taken with an in-field ruler (Puritan stick) are subject to a central blinded review. Training of site investigators is provided during site initiation visits and updates. In cases of trismus, clinical photographs are facilitated by intra-oral cameras which are available with disposable single use covers. Digital copies of the clinical photographs (with in-field rulers) are securely uploaded to the study database by the site staff. At the end of the trial, the central review panel will be provided with the anonymised clinical photographs by the Liverpool Clinical Trials Centre (LCTC) from baseline and 12 months (and at study completion for patients who continue beyond 12 months) for blinded assessment. The outcomes within the patient preference arm of the trial (i.e. after 12 months) will be considered and presented separately. Quality control of images and radiographs from each site is performed from the first images returned and a random sample thereafter.

The secondary outcomes measures include the determination of the impact of PENTOCLO on the deterioration of ORN, analgesia and antibiotic usage, quality of life (using EORTC QLQ-30), mandibular preservation, anthropological measurements, safety, tolerability and compliance of trial medications (complete list Table 2).

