## Statistical methods

### Statistical methods for primary and secondary outcomes {20a}

The primary outcome is time to healing. Healing rates will be estimated using the method of Kaplan and Meier. Comparisons across treatment groups will be performed using a log-rank test. Further analysis adjusting for key demographic and clinical covariates will be performed using a Cox proportional hazards model. The primary analysis will be carried out on the full analysis set, which will be defined on the intention to treat principle, retaining patients in their initially randomised groups irrespective of any protocol violations. Analysis of the primary outcome will be assessed using 1-tailed 0.1 level, as is consistent with the type I alpha level used in the study design. The one-sided test is employed in order to limit sample size and in the light of previous systematic reviews where no detriment to healing from PENTOCLO has been reported. All analyses of secondary outcomes will use the nominal *p* < 0.05 level to determine statistical significance. Full details of all planned analyses will be specified in a statistical analysis plan, which is provided as Appendix 1 (supplementary data).

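### Censoring treatment failures makes Kaplan-Meier overstate the share of patients healed at 12 months, and the log-rank test does not compare the 40% and 60% healing proportions on which the design is framed

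*Protocol article*

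**What the plan says.** The outcome is defined in Outcomes {12}: "The primary outcome measure is time from randomisation to healing of ORN (without the need for surgery), as measured by" clinical examination, photographs and radiographs. The same section then says: "Conversely, patients who demonstrate failure of treatment as below will be treated as censored observations". Its two categories are deterioration of ORN including fracture, and a clinical indication for resection and reconstruction. It adds that complete healing and "mandibular fracture or other clinical indication to progress to surgery within 12 months both constitute a primary endpoint for that patient", and that patients whose ORN persists without surgery reach the primary endpoint at 12 months.

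Statistical methods {20a} fixes the analysis: "Healing rates will be estimated using the method of Kaplan and Meier", and "Comparisons across treatment groups will be performed using a log-rank test", followed by an adjusted Cox model. The section Worsening ORN explains why resection ends participation: "After this surgery, it is presumed that there will no longer be remaining necrotic bone to monitor on trial".

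The article mentions no competing-risk method. It gives no expected failure rate for this trial. The one frequency available comes from the second systematic review in Background {6a} (186 patients on PENTOCLO): "ORN was stable or progressive in 60 patients, with 15 patients receiving jaw resections".

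**The concern.** Kaplan-Meier treats a censored patient as someone who would go on to heal at the same rate as those still under observation. That suits a patient lost to follow-up for unrelated reasons. It does not suit a patient sent to resection, for whom healing without surgery is no longer possible. Such patients are also removed because their ORN got worse, so they are not a random sample of those at risk. The resulting curve describes healing in a setting where nobody fails, not the share of randomised patients who heal.

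Two things are at stake. The first is the reported 12-month healing rate in each arm, and with it the effect size that Objectives {7} wants for a later definitive trial. The second is what the comparison between arms means. Site staff know the allocation (Concealment mechanism {16b}), and the abstract hopes PENTOCLO will reduce major surgery. Unequal failure rates are therefore plausible, and part of what the trial hopes to see.

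**Working it through.** **Inputs.** Healing of 40% and 60% at 12 months, hazard ratio 0.56, one-sided alpha 0.10, power 90%, 78 events, 120 patients and 5% attrition all come from Sample size {14}. The only failure anchor is 15/186 = 8.1%. All other failure rates are assumptions, within a range of 5% to 30%.

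**The plan's own figures.** ln(0.60)/ln(0.40) = 0.5575, stated as 0.56. Schoenfeld events = (1.2816 + 1.2816)² / (0.25 × (ln 0.56)²) = 78.2, stated as 78. Both reproduce. The conversion from 40% and 60% to a hazard ratio treats 1 minus the share healed as the survival function, which is correct only if nobody has a competing event.

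**Overstatement of the share healed.** Let h be the true share healed and f the share failed by month 12, with constant cause-specific hazards.
- Total cumulative hazard: Λ = −ln(1 − h − f)
- Healing part: Λh = Λ × h/(h + f)
- Kaplan-Meier reading with failures censored when they occur: 1 − exp(−Λh)

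Example, h = 0.40 and f = 0.08: Λ = −ln(0.52) = 0.654; Λh = 0.654 × 0.40/0.48 = 0.545; reading = 42.0%.

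| True share healed | f = 8% | f = 15% | f = 25% | f = 30% |
|---|---|---|---|---|
| 40% | 42.0% | 44.1% | 47.6% | 49.7% |
| 60% | 63.4% | 67.0% | 73.8% | 78.5% |

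A true difference of 20 points reads as 63.4 − 42.0 = 21.4 points with 8% failures in both arms. It reads as 63.4 − 47.6 = 15.8 points with 25% failures in control and 8% on PENTOCLO.

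**What the log-rank test compares.** With failures censored, it compares the cause-specific hazards of healing.
- Healing 40% in both arms, failures 10% in A and 30% in B: Λh is 0.555 and 0.688, a ratio B to A of 1.24. Equal proportions healed are therefore not equal hazards.
- Healing 40% v 60%, failures 25% v 8%: Λh is 0.646 and 1.005, a ratio of 1.56, against the design's 1/0.5575 = 1.79.

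**Simulation.** 57 per arm (120 × 0.95 / 2), 3-monthly visits, one-sided 0.10, 3000 replicates, Monte Carlo standard error at most 0.9 points. Entries are the percentage of trials declaring B superior.

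| A healed/failed | B healed/failed | Failures censored | Failures kept as not healed to month 12 |
|---|---|---|---|
| 40/10 | 40/20 | 15.8 | 10.5 |
| 40/10 | 40/30 | 23.4 | 11.3 |
| 40/20 | 60/8 | 75.0 | 81.3 |
| 40/25 | 60/8 | 69.6 | 80.2 |
| 40/10 | 60/10 | 84.7 | 81.9 |
| 40/15 | 60/15 | 86.6 | 83.2 |

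Nearer the anchor, with healing 40% v 60%, power is 83.5 v 82.1 (failures 8% v 8%), 81.6 v 82.3 (12% v 8%) and 79.4 v 81.3 (15% v 8%). With healing 40% and failures 8% in both arms, rejection is 10.6% under either method. Power sits below 90% throughout because 57 per arm at these rates gives about 57 × (0.40 + 0.60) = 57 healings, not 78; that is a separate matter.

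**The case against.** The strongest reply is that a log-rank test with failures censored is a legitimate test of the cause-specific hazard of healing, so the issue is which quantity to target. That stands. A reader might infer from the 23.4% above that the test loses its type I error. It does not: the cause-specific hazards in that scenario have a ratio of 1.24, so the null of that test is false there. The figure shows only that the test answers a different question from whether more patients heal.

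The large effects also need assumed failure rates that are unequal and well above 8%. Near the anchor the choice of test barely matters, and with equal failures the planned test is slightly more powerful. That stands too. The anchor itself is limited: it counts resections only, in treated patients, whereas the trial's failure category also includes fracture and other deterioration.

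A reader might further infer that both design rates come from published series that kept resected patients in the denominator. Sample size {14} attributes only the 60% to the literature; the 40% is a judgement. It also does not say which review supplies the 60%.

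Nor is it a firm contradiction that failures are censored and yet "both constitute a primary endpoint for that patient". Patients with persisting ORN are also said to reach the primary endpoint at 12 months, so the term seems to mean the end of primary observation. The wording is loose.

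Finally, time to worsening and mandibular preservation are secondary outcomes in Table 2, so an imbalance in failures would be visible. The separate analysis plan may also add a competing-risk analysis. Neither changes the estimator and censoring rule that the article states for the primary outcome.

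**Conclusion.** The concern holds for the estimator. Where resection rules out the endpoint, 1 minus Kaplan-Meier overstates the share healed: by 2.0 points at a true 40% and 3.4 points at a true 60% with 8% failures, rising to 9.7 and 18.5 points with an assumed 30%. These figures assume constant hazards and censoring at the time of failure. The article does not state the censoring time, and censoring failures at month 12 would remove the overstatement that they cause.

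For the test the conclusion is narrower. It is valid for the hazard it tests, but it does not compare the proportions healed. It can drift from them in either direction if failure rates differ by arm, and the article does not say how large such a difference would be.

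The censoring list is also too broad. Deterioration short of fracture or an indication for surgery does not rule out later healing, yet Outcomes {12} censors it.

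**What to change.** In Outcomes {12} and Statistical methods {20a}:

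1. Report 12-month healing in each arm as cumulative incidence (Aalen-Johansen), with fracture, indication for resection, and death before healing as competing events. Show the cumulative incidence of failure beside it.
2. Compare the arms with failures kept as not healed to month 12, by Gray's test or a log-rank test with failures censored at month 12. Make this the primary test, or at least a pre-specified analysis beside the cause-specific log-rank and Cox. Patients lost for other reasons stay censored at their last visit.
3. Do not censor patients whose ORN deteriorates without fracture or an indication for surgery; follow them for healing to month 12.
4. State the censoring time, and reword the primary endpoint sentence so that it is clear which outcomes are events and which only end primary observation.

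Items 1 and 4 need wording only and use data already collected. Item 3 relies on the scheduled 3-monthly visits. Item 2 costs about 3 points of power if failures are equal in both arms (84.7 to 81.9 at 10%, 86.6 to 83.2 at 15%). If it replaces the primary test, it changes the primary analysis of an open-label trial recruiting since April 2023, so it should be documented as an amendment before any comparison by arm is seen.
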